## Methods

### Overview

This protocol was created following the SPIRIT (Standard Protocol Items: Recommendations for Interventional Trials) reporting guidelines (Multimedia Appendix 1) [42]. The proposed study is a randomized comparison trial to evaluate the acceptability, appropriateness, and feasibility of uTECH, which is a text-based risk reduction intervention that leverages a data mining and ML algorithm to provide personalized prevention messaging to users. uTECH will be compared to an existing best-evidence MI intervention (YMHP). Participants will be randomly assigned to one of two conditions: (1) uTECH+YMHP (trial intervention+existing intervention) or (2) YMHP only (existing intervention only). Those in the uTECH+YMHP condition will receive 4 YMHP sessions with a trained master’s-level social worker and tailored SMS text messages. Those in the YMHP arm will only receive 4 YMHP sessions. Participants in both conditions will either contribute location-tracking and keylogger smartphone data through an app called “eWellness” (version 1.0.24) or provide data downloads from their most-used, web-based dating and social media accounts. These data will be used to inform and prime the ML algorithm that will be used to make predictions and generate tailored SMS text messages for the uTECH+YMHP condition. The overarching goal of this study is to evaluate the acceptability, appropriateness, and feasibility of uTECH in conjunction with YMHP (condition 1) compared to YMHP alone (condition 2). This study was registered with ClinicalTrials.gov under NCT04710901.

### Target Population

This study aims to recruit 330 participants. Half (n=165, 50%) of the participants will be randomized to receive uTECH+YMHP (condition 1), and the remaining half (n=165, 50%) will be randomly assigned to receive YMHP only (condition 2).

To be eligible for the study, participants must be aged 18 to 29 years, identify as SGM, have had anal or oral sex with a man (defined by the participant’s interpretation) in the past 3 months, have used substances (such as alcohol, marijuana, amyl nitrate [poppers], methamphetamines, heroin, cocaine, and ecstasy) in the past 3 months, have had sex while using substances in the past 3 months, have a negative or unknown HIV status, and have used a dating app to meet sexual or substance use partners in the past 3 months. Participants must also own a smartphone, reside in the United States, be willing to participate in a 12-month study, and be able to provide informed consent. Participants that use an Android smartphone as their primary device must consent to install the eWellness app on their phone to remotely collect keystroke and geolocation data throughout the duration of the study. Participants who use an iOS (Apple Inc) smartphone must provide the study team with at least 1 set of data from both their primary dating app and their most-used social media account every 6 months. Failing to meet all the stated criteria would disqualify individuals from enrollment in the study. Exclusion criteria were conceived to build upon existing literature for HIV prevention in SGM populations while also expanding gender criteria to be inclusive of transgender and gender nonbinary individuals who have sex with men. Our study population aims to capture the identities of young adult users of queer-centered dating apps and websites such as Grindr, Scruff (Perry Street Software, Inc), and Sniffies (Sniffies, LLC) who may be at heightened risk of HIV and STI transmission [17-19], particularly in the context of substance use [5-9].

### eWellness App Development

The mobile app, eWellness, was developed during phase 1 of this study and uses the AWARE framework [43], which is an open-source context instrumentation that uses smartphone sensor instruments to infer, log, and share mobile information for application developers and researchers. The AWARE framework has been used in numerous earlier eHealth studies, for example, to predict depression and anxiety [44,45], progression of Parkinson disease [46], or alcohol use events [47]. We developed eWellness using the AWARE framework and dashboard to record keylogging data (data entered into the user’s preferred smartphone keyboard), which are remotely downloaded to secure databases daily. eWellness is also enhanced with a user-friendly interface that provides several “tabs” of information, including a study timeline and incentive chart; a brief survey; and an interactive Google-based map of nearby HIV and STI testing locations, risk reduction supportive services, needle exchanges, and other harm reduction and substance use treatment services.

The data collected through the eWellness app are used to refine and “teach” the ML algorithm to make predictions that can be used to inform the uTECH intervention. During the 12-month design process, we developed a working version of the app and added additional features as they were developed. We recruited SGM people (n=20) aged >18 years who used Android phones and used websites and apps to seek sexual or substance use partners. These phase-1 participants downloaded the app, which collected data that were used by the study team to further refine the ML algorithm.

Throughout the 12-month study, we also conducted semistructured interviews with the participants to obtain feedback and preferences on possible app functions. Interviewers followed a questionnaire developed by the principal investigator and research staff. Data from these phase-1 interviews were analyzed using rapid qualitative analysis [48], and insights were used to refine and finalize the app in preparation for phase 2.

During phase 2, the eWellness app will be installed by participants who use Android smartphones. Once installed, the app will collect data continuously for 12 months. The app collects the following data: keystrokes (letters and numbers that the user types into their smartphone keyboard), the time and date of information that is typed into the keyboard, the name of the app used when typing in an app, and geolocation. The app does not collect the following data: any data that are not typed directly into the smartphone keyboard, photos or camera data, accelerometer data, video, drop-down menu selections, barometer, audio or microphone data, battery data, text-to-speech data, Bluetooth data, address book contacts, gyroscope data, screen time tracking data, gravity sensor data, incoming SMS text messages, magnetometer data, phone logs, proximity sensor data, installation logs, scheduler data, network sensor availability, temperature data, rotation sensor data, Wi-Fi data, telephony data, or time zone data.

### Social Networking App Downloads

Participants who use iOS smartphones will be asked to provide social networking app account downloads from their most frequently used web-based dating apps, such as Grindr or Tinder, and social media accounts, such as Twitter or X (X Corp), Instagram (Meta Platforms, Inc), Reddit (Reddit, Inc), and Facebook (Meta Platforms, Inc), to send to the research team. The data requests will occur at baseline and at 6-month and 12-month follow-up interviews. The exact data request process varies for each app but generally involves the user going into the app settings and requesting a data download that will be sent to the participant’s email address. The participant then downloads their data and emails the files to an encrypted email address managed by the research team.

Data requests may include but are not limited to text-based content of social media posts, profile information, chats and messages they send to others, like or viewing history, advertisement history, and background activity (such as time spent on the app, geolocation, and account settings).

### YMHP Intervention

The YMHP intervention consists of four 1-hour counseling sessions that use MI as a collaborative, goal-oriented approach of communication to discuss how participants manage sexual health and substance use in their daily lives. The goal of the YMHP counseling sessions is to explore these issues while supporting participants in making informed decisions for their health [36]. The sessions will be conducted by doctoral students trained in YMHP, holding master’s degrees in social work, and supervised by a licensed clinical social worker.

There is a wealth of evidence demonstrating the effectiveness of MI for behavioral change [49]. MI is rooted in the principles of engaging, focusing, evoking, and planning. The practice and implementation of MI use deep listening skills, effective reflections, and strategies for responding to resistance. Engaging involves building rapport and creating a sense of alliance through approaching participants with an attitude of curiosity, compassion, and understanding. Focusing involves exploring the participant’s view of their situation and selecting a target behavior for change. Although the main target behaviors are sexual health and substance use, understanding the participant’s priorities and goals is essential. Evoking is the act of finding out the participant’s own reasons for change and brainstorming how to reach those goals. Evoking can be achieved using open-ended questions and the Ask-Tell-Ask method [50]. Planning involves the creation of a course of action and the anticipation of obstacles. The transition into the planning stage should only be done when the participant is ready and willing to do so.

For this study, YMHP will be tailored and used with young adults across the SGM spectrum and will include gay and bisexual men as well as transgender women, transgender men, and gender nonbinary individuals who have sex with men, reflecting our study population.

### The uTECH Intervention

Participants randomized to receive the uTECH intervention (uTECH+YMHP) will receive SMS text messages that use the Information-Motivation-Behavior Skills (IMB) model [51] to improve substance use harm reduction and promote safer sex practices. The IMB model was developed to use information, motivation, and behavioral skills to promote HIV-related behavior change, positing that when groups at risk for HIV are well informed, motivated to act on their knowledge, and have the necessary behavioral skills to seek out and initiate change, they will successfully overcome obstacles to make behavior change. The IMB model is effective in enhancing protective health behaviors such as adherence to interventions or reduction of risk behaviors with people living with HIV or AIDS [52-54] and people who use substances [55-57].

Staff will follow the IMB framework to generate content for the SMS text messages, a process that will be informed by an extensive review of public health messaging, scientific literature, and validated survey instruments tailored for specific subgroups that will be recruited for this study. The groups include people who inject drugs, people who do not inject drugs, people who are on PrEP, people who are not on PrEP, transgender and nonbinary people who are on PrEP, and transgender and nonbinary people who are not on PrEP. Each participant will be assigned to 1 of the above subgroups based on their answers in their baseline interview. The SMS text messages will be sent to participants using Twilio (version 8.0.0; Twilio Inc) [58], a web-based communications service that can be programmed to send and receive SMS text messages. Approximately 2 SMS text messages will be scheduled per week, so that each participant will receive 100 text messages over the course of 12 months.

To obtain feedback, participants will be asked to respond to each SMS text message. Participants will be compensated US $1 per SMS text message to which they reply. Each SMS text message also includes an opt-out option to comply with cell carrier antispam policies. The feedback from participants will also be used to enhance the ML algorithm in preparation for fully automated SMS text message generation and assignment (Table 1).

**Table 1 table1:** Text message content examples from the uTECH intervention using the Information-Motivation-Behavior Skills (IMB) model.

	PrEP^a^ initiation	PrEP adherence	Sexual risk reduction	Substance use harm reduction
Information	“PrEP reduces the risk of getting HIV from sex by approximately 99%—if taken on an ongoing basis before sex and continued after sex. It is also called Truvada or Descovy.”	“Did you know? The Food and Drug Administration approved injectable PrEP, which is an option for people who are tired of taking a pill every day. It is an injection given every 2 months. Find out more at: https://www.fda.gov/news-events/press-announcements/fda-approves-first-injectable-treatment-hiv-pre-exposure-prevention.”	“If you had unprotected sex, you can take PEP (postexposure prophylaxis) up to 72 hours after possible exposure to prevent HIV. Watch a video to learn more: https://www.youtube.com/​watch?v=Yu82TFo6j94&featu”	“Here is a tip for staying hydrated while drinking: drink 1 glass of water for every alcoholic beverage you have. This is known as the 1-for-1 rule and may help moderate your drinking and lessen the chance of a hangover.”
Motivation	“Did you know that studies show taking PrEP lowers HIV-related anxiety? Are you less anxious about HIV when you are on PrEP?”	“Did you know that studies show taking PrEP lowers HIV-related anxiety? Are you less anxious about getting HIV when you are on PrEP?”	“Nervous about getting STI^b^ testing? It is safer to get tested and know the results. Here is how others overcame their concerns about STI testing: https://www.youtube.com/​watch?v=rN5d_XQKRxg.”	“If you ever inject with a friend, you could consider doing so at a SIS^c^. SIS refers to places where people who use injectable, but illegal, opioids such as heroin can do so without fear of overdose, prosecution, or spreading disease. You can try looking up sites in your area to find them or contact a member of the research team for assistance.”
Behavior	“Reply with the number of the statement that applies to you: 1. I have talked to a medical provider about getting PrEP but have not yet started taking it. 2. I have already talked to a medical provider about getting PrEP and have begun taking it. 3. I have not talked to a medical provider about getting PrEP and have not taken it yet.”	“Reply with the number of the statement that applies to you: Have you at any point considered stopping PrEP? 1. No, I am happy with PrEP and expect to continue taking it. 2. No, I am neither happy nor unhappy with PrEP, it just does not seem like an option to stop PrEP use. 3. Yes, but I changed my mind and expect to continue taking it. 4. Yes, and I did stop use for a period of time. Since then, I have resumed and plan to continue taking it. 5. Yes, and I am planning on discontinuing use soon.”	“Reply with the number of the statement that applies to you: 1. In the past month, I have gotten tested for HIV or ≥1 STIs. 2. In the past month, I have not gotten tested, but I have booked an appointment or set a date to get tested in the near future. 3. In the past month, I have not gotten tested and currently do not have an appointment or plan to do so.”	“Reply with the number of the statement that applies to you: Have you ever trusted someone to supervise you (or trip-sit) as you inject for safety purposes? 1. Yes, always. 2. Yes, but only once or a few times. 3. Yes, but I would not do it again. 4. No, but I would like to in the future. 5. No, I do not feel comfortable being supervised.”

^a^PrEP: pre-exposure prophylaxis.

^b^STI: sexually transmitted infection.

^c^SIS: safe injection site.

### Recruitment

#### Web-Based Outreach

Participants will be recruited through web-based outreach methods including targeted advertising on social media sites (ie, Meta, Grindr, Craigslist [Craigslist Inc], and Reddit), with a focus on Facebook Pages and Groups, or forums that may attract SGM individuals who use substances. The research team will also contact community organizations and prominent users with high follower counts to broaden recruitment efforts on social media sites such as OnlyFans (OnlyFans Ltd) and Instagram.

#### In-Person Outreach

The research team will distribute recruitment materials such as business cards, flyers, and palm cards at events that may attract SGM individuals who use substances; sexual health clinics; lesbian, gay, bisexual, transgender, and queer centers; substance use treatment centers; nonprofit organizations; and retail businesses. Staff will reach out to community-based organizations and retail businesses by phone and email, offering to mail recruitment materials to display at their locations to broaden recruitment nationwide.

#### Referral Program

Both participants and nonparticipants will be given the opportunity to refer others to the study and receive compensation for their referrals. Those interested in the referral program will be given information about the study, a sample message to send to others for referral purposes, and a link to sign up as a referrer so that the study staff can compensate them. Participants will be offered the opportunity to receive physical recruitment materials by mail (flyers and palm cards) to refer people within their social networks. Referrers will receive US $20 sent to their payment method of choice (Venmo [PayPal Holdings Inc], Cashapp [Block Inc], Paypal [PayPal Holdings Inc], or Amazon [Amazon Inc] e-gift card) for every person referred into the study that completes their baseline appointment (up to 5 people total).

### Enrollment Process

#### Screening

All participants will first complete a web-based screener survey on Qualtrics (Qualtrics International Inc), a web-based survey platform [59]. The screener will provide information about the study and ask the participant questions to determine eligibility and their willingness to provide keystroke and geolocation data (Android users) or social media data (iOS users). If the potential participant meets initial eligibility criteria, the survey will use branching logic to show additional screens for the individual to provide contact information, including email address and phone number.

Research staff will review screener responses daily and closely examine responses to check for fraudulent or false eligibility. Qualtrics collects users’ geolocation information and IP addresses, which will be used to input into a third-party fraud-checking website, such as Scamalytics [60]. The information we receive from Qualtrics will be checked using such websites to determine whether their phone number is a voice-over IP (or noncellular, internet) number or whether their IP address has been blacklisted for fraudulent activity or uses virtual private network, which would enable non-US users to bypass geolocation-based restrictions. “Eligible” screened participants who use a voice-over IP or virtual private network or come from an IP address with high fraudulent activity will be coded as “fraud” and will not be contacted by study staff.

Those who submit screeners that appear legitimate and who are eligible according to study criteria will be contacted by research staff via phone call, email, or SMS text message to schedule an onboarding. Participants will be provided a link to Calendly [61], a web-based calendar scheduling service, to pick a time for their onboarding session and will receive automated reminders for their appointments once booked. All appointments will take place over the Zoom videoconferencing platform. The interviewer will confirm that the participant will be in a safe and private setting to talk about confidential information for the duration of the call before beginning the session.

#### Randomization

All eligible participants will have their information entered into a password-protected and encrypted database that is only accessible by Health Insurance Portability and Accountability Act–certified and institutional review board–approved research staff. Alongside contact information, all participants will be assigned a participant ID number and computer-generated randomized assignment to 1 of 2 intervention groups: uTECH+YMHP or YMHP only. This randomization will be done before onboarding so that the onboarding study staff will know which type of onboarding will be required.

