#### Consenting (All Participants)

The interviewer will open the appropriate consent form for the participant’s phone type (Android or iOS) and study condition (uTECH+YMHP or YMHP only), which is a survey hosted on Qualtrics, and share their screen on Zoom so that the participant can view it simultaneously. The interviewer will remind the participant that they will receive a copy of the document via email at the end of the call. The interviewer will input the participant ID at the top of the page and review study details while regularly asking the participant if they have any questions. The consent form includes a detailed explanation of all study requirements and how their data will be protected. At the end of the consent form, the interviewer will ask if the participant consents to the study. If affirmative, the interviewer will check the box for “I agree to participate in the study,” provide their initials on the survey, and submit the consent survey. If the participant does not consent, then the interviewer will check the box for “I decline to participate in the study,” provide their initials on the document, submit the survey, thank the participant for their time, and end the call. The consent process will take approximately 25 minutes. If the participant consents to participate, then the onboarding session will continue.

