### Incentives

Incentives vary according to intervention and phone type (Figure 1). Participants assigned to the YMHP-only condition will receive US $350, and participants assigned to the uTECH+YMHP condition will receive US $450, including responses to all uTECH messages. The payments for baseline (US $30), 6-month (US $40), and 12-month (Android: US $50; iOS: US $55) interviews are escalated to promote retention in the study. Participants will be paid for each study activity to encourage engagement.

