### Ethical Considerations

The research and ethics presented in this study were reviewed and approved by the South Campus institutional review board of the UCLA (#22-000009). The research has also been granted a Certificate of Confidentiality from the National Institutes of Health (CC-OD-22-3555), which deems identifiable information gathered in the course of research not admissible as evidence in any legal processes. Additional terms were provided to ensure confidentiality for the participants. These terms included protection for all study-related data obtained by all uTECH study staff, which includes employees, students, interventionists, and other professionals staffing the project. All participant data will be deidentified and accessible only to staff who completed training in Health Insurance Portability and Accountability Act guidelines and human participants research ethics.

Technical concerns related to data privacy were considered throughout the app development process, which occurred during phase 1 of this project. In collaboration with the UCLA Information Technology and UCLA Compliance departments, considerations related to data storage and data in transit were considered, including the institution’s legal and ethical duties related to the handling of personally identifiable information. Procedures and protocols were established in collaboration with the UCLA Technology Development Group and the UCLA Departments of Computer Science and Engineering.

To enroll in the study, participants would have to review and consent to a study consent form detailing all activities associated with study participation; potential risks and benefits to participation; incentives; and privacy or confidentiality protections granted by the National Institutes of Health Certificate of Confidentiality, UCLA Office of Human Research Protection Program, and study investigators. Participants will be informed during the consenting process that all payments will be made via e-gift card disbursement with a breakdown of all payments totaling the amount of US $350 or US $450 depending on the study group assignment and phone type.

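### Arm is assigned before consent and baseline, and the consent form and payment total depend on the arm, so refusal can depend on allocation and the planned baseline check cannot see it

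*Protocol article*

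**What the plan says.** The order of procedures has to be put together from several sections of the protocol article.

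- **Randomization.** Once a person is screened as eligible, "all participants will be assigned a participant ID number and computer-generated randomized assignment to 1 of 2 intervention groups". The timing is explicit: "This randomization will be done before onboarding so that the onboarding study staff will know which type of onboarding will be required".
- **Consenting (All Participants).** The interviewer selects the form by "phone type (Android or iOS) and study condition (uTECH+YMHP or YMHP only"). Refusal is provided for ("If the participant does not consent, then the interviewer will check the box for" declining) and ends the call. Otherwise, "If the participant consents to participate, then the onboarding session will continue".
- **Incentives.** "Participants assigned to the YMHP-only condition will receive US $350, and participants assigned to the uTECH+YMHP condition will receive US $450". Ethical Considerations adds that the payment breakdown, with a total set by study group and phone type, is given during the consent process.
- **Ethical Considerations.** Enrolment itself depends on consent: "To enroll in the study, participants would have to review and consent to a study consent form".
- **Baseline Interview.** The interviewer administers the baseline survey on a shared screen later in the same session. It covers sexual health and substance use, among other topics.
- **Missing Data.** Baseline data are to be used to judge whether randomisation balanced the groups, to study differential attrition, and to supply adjustment covariates if balance fails.

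**The concern.** Randomisation protects the comparison only for the people who were randomised. Here a decision point, consent, lies between randomisation and entry, and it is taken with an arm-specific form on the screen. Someone put off by the text-message component can leave one arm and not the other. Someone attracted by the larger total can enter one arm and not the other.

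This matters more than usual because acceptability is a primary outcome. Declining after seeing what one's own arm involves is close to a direct statement of low acceptability, so the selection may act on the outcome itself.

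The planned safeguard starts too late. Balance and attrition are both assessed from baseline onward, in consenters, after the arm has been disclosed. Losses at the consent step are invisible to it, and adjustment for baseline covariates cannot restore people who are not in the data.

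**Working it through.** **Step 1. Sequence.** Setting the sections in order gives: screener and fraud check; assignment; onboarding call with staff aware of the arm; arm-specific consent form and payment total; consent or refusal; baseline. The article describes no step that withholds the arm until consent and baseline are complete.

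**Step 2. Does anything need the arm that early?** Apart from consent, the onboarding steps either differ by phone type (app installation, data downloads, Wellness Survey) or apply to everyone (PrEP verification, baseline, YMHP scheduling, close-out). Text-message subgroups are set from baseline answers. The one described step that needs the arm before baseline is the arm-specific form itself.

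**Step 3. The payment gap.** 450 − 350 = US $100. The uTECH Intervention section gives 100 messages at US $1 per reply: 100 × 1 = US $100. The gap is fully explained by payment for an added task, but it is still an arm difference shown before the decision to consent.

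**Step 4. Possible size.** The article gives 424 enrolled but not the numbers randomised or declining by arm, so there is no figure to reproduce. The following inputs are assumptions, except that 85% is borrowed from the power calculation:

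- acceptability is 85% in both arms, with no true difference;
- 30% of eligible people are averse to this kind of messaging and have 65% acceptability;
- the other 70% then have (0.85 − 0.30 × 0.65) / 0.70 = 0.655 / 0.70 = 93.6%;
- a fraction *d* of the averse group declines, and only when shown the uTECH+YMHP form.

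Acceptability among uTECH+YMHP consenters = [0.30(1 − *d*) × 0.65 + 0.655] / [1 − 0.30*d*].

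| *d* | Share of arm lost | Acceptability among consenters | Spurious difference | Difference if decliners count as not accepting |
|---|---|---|---|---|
| 10% | 3% | 0.8305 / 0.97 = 85.6% | +0.6 points | 83.05 − 85 = −1.95 |
| 30% | 9% | 0.7915 / 0.91 = 87.0% | +2.0 points | 79.15 − 85 = −5.85 |
| 50% | 15% | 0.7525 / 0.85 = 88.5% | +3.5 points | 75.25 − 85 = −9.75 |

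If the same people instead decline only in the YMHP-only arm, for example because the larger total keeps them in the other arm, the spurious difference is the mirror image, −0.6 to −3.5 points.

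**Step 5. Yardstick.** The Sample Size section aims at 9 points (autocorrelation 0.1) or 11 points (0.5). The largest illustrated shift is 3.5 / 9 = 39% or 3.5 / 11 = 32% of that; the smallest is 0.6 / 9 = 7% or 0.6 / 11 = 5%.

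**The case against.** The case on the other side has real weight.

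- **The arms are alike in most of what might deter people.** Twelve months of keystroke and location capture, or social-media downloads, applies to both arms, and willingness to provide these data is asked at the screener, before assignment. Both arms have the same four counselling sessions. What differs is about two texts a week, each with an opt-out, and pay per reply. A large gap in refusal is therefore not the obvious expectation. This stands, and it argues for the lower part of the range.
- **Baseline plays a limited part in the primary comparison.** Primary outcomes are measured at 3, 6, 9 and 12 months, and the growth models use those visits. Demographics will hardly change with knowledge of the arm. This also stands. The exposure at baseline is confined to self-reported behaviour used for balance checks or as covariates. It does not answer the point about refusal.
- **Flow counts belong in the results report.** Their absence from a protocol article is no fault. The point here is the order of procedures, which the article fixes and no analysis plan can reverse.

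A reader might go further and infer that missed onboarding appointments also differ by arm because of allocation. The documents do not support that. They say onboarding staff know the arm, not that invitees learn it before the consent form is opened, and they describe no difference in follow-up by staff.

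**Conclusion.** The point holds as a design weakness that should be addressed, not as a demonstrated bias. The documents establish that allocation precedes consent and baseline, that the form and disclosed payment differ by arm, and that the planned balance check rests on consenters after disclosure. Entry and self-reported baseline behaviour can therefore depend on allocation, and the planned check would not show it.

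Size and direction are unknown. The range of about 0.6 to 3.5 points rests entirely on assumed inputs and could have either sign. It is smaller than the 9 to 11 point target but not negligible beside it.

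Three stronger conclusions should be resisted. A reader might say that selection bias has occurred; without refusal counts by arm, nothing shows that. A reader might recompute a smaller detectable difference and call 3.5 points more than half of it; the protocol states only 9 to 11 points, and a recomputed value depends on the autocorrelation chosen. A reader might accuse the authors of mislabelling an intention-to-treat set; the article does not use that term. If refusals prove few and balanced, the concern is largely answered.

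**What to change.** **Completed cohort** (enrolment and data collection are over; analysis is under way):

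1. Report by arm the numbers randomised, attending onboarding, declining and consenting.
2. Compare screener variables, which predate assignment, between arms and between consenters and non-consenters.
3. If refusal differs by arm, add a sensitivity analysis for entry: inverse-probability weighting on the available screener variables, or bounds that count decliners as not finding the intervention acceptable.
4. Describe the analysed set as those who consented after randomisation.

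**Further enrolment or a successor trial:** use one consent form describing both arms, then the baseline survey, then release of the computer-generated assignment in the same call.

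**Cost.** For this trial, one flow table and a small amount of extra analysis. Weighting removes only measured selection. The screener may offer few useful variables, since everyone randomised met its criteria, and the article does not say whether decliners' screener data are kept. Bounds avoid that dependence but can be wide, as the last column of the table shows. For a later trial, the cost is a reordering of steps within one call and a single form in place of the arm-specific ones.
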